# A two arm randomized controlled trial comparing the short and long term effects of an elimination diet and a healthy diet in children with ADHD (TRACE study). Rationale, study design and methods

**DOI:** 10.1186/s12888-020-02576-2

**Published:** 2020-05-27

**Keywords:** ADHD, Children, Dietary treatment, Short and long-term effects, Cost-effectiveness

## Abstract

**Background:**

Food may trigger Attention-Deficit/Hyperactivity Disorder (ADHD) symptoms. Therefore, an elimination diet (ED) might be an effective treatment for children with ADHD. However, earlier studies were criticized for the nature of the control group, potential confounders explaining the observed effects, unsatisfactory blinding, potential risks of nutritional deficiencies and unknown long term and cost-effectiveness. To address these issues, this paper describes the rationale, study design and methods of an ongoing two arm randomized controlled trial (RCT) comparing the short (5 week) and long term (1 year) effects of an elimination diet and a healthy diet compared with care as usual (CAU) in children with ADHD.

**Methods:**

A total of *N* = 162 children (5–12 years) with ADHD will be randomized to either an ED or a healthy diet. A comparator arm including *N* = 60 children being solely treated with CAU (e.g. medication) is used to compare the effects found in both dietary groups. The two armed RCT is performed in two youth psychiatry centers in the Netherlands, with randomization within each participating center. The primary outcome measure is response to treatment defined as a ≥ 30% reduction on an ADHD DSM-5 rating scale (SWAN) and/or on an emotion dysregulation rating scale (SDQ: dysregulation profile). This is assessed after 5 weeks of dietary treatment, after which participants continue the diet or not. Secondary outcome measures include the Disruptive Behavior Diagnostic Observational Schedule (DB-DOS), parent and teacher ratings of comorbid symptoms, cognitive assessment (e.g. executive functions), school functioning, physical measurements (e.g. weight), motor activity, sleep pattern, food consumption, nutritional quality of the diet, adherence, parental wellbeing, use of health care resources and cost-effectiveness. Assessments take place at the start of the study (T0), after five weeks (T1), four months (T2), eight months (T3) and 12 months of treatment (T4). T0, T1 and T4 assessments take place at one of the psychiatric centers. T2 and T3 assessments consist of filling out online questionnaires by the parents only.

**Discussion:**

This RCT will likely contribute significantly to clinical practice for ADHD by offering insight into the feasibility, nutritional quality, (cost-)effectiveness and long term effects of dietary treatments for ADHD.

**Trial registration:**

www.trialregister.nl, NTR5434. Registered at October 11th, 2015.

## Background

Attention-Deficit/Hyperactivity Disorder (ADHD) is a neuropsychiatric disorder that affects about 7.2% of children and adolescents [1]. Both genetic and environmental factors contribute to the development of ADHD [2]. Treatment for ADHD includes psychoeducation, child behavioral interventions, parent training and medication. However, long-term beneficial effects of these treatments have not been convincingly established [3, 4], and there is also a growing concern about increasing prescription rates of medication and potential long-term side-effects [5–7]. Therefore, the present study focuses on a non-pharmacological intervention for children with ADHD, namely a dietary intervention.

There is a growing awareness that diet may play a role in psychological well-being and psychiatric disorders like ADHD [8–10]. Results of two meta-analyses and one recent review study [11–13] demonstrate that the so-called elimination diet (ED) showed the largest effects. For 30% of children an ED was effective in reducing ADHD symptoms [14]. The rationale for an ED is that a patient with ADHD may show adverse reactions to certain types of food. The ED involves a temporary (two-five weeks) total change of diet in which the patient is allowed to eat only a limited number of different hypo-allergenic foods (e.g. rice, turkey, lettuce and pears). After a significant reduction of ADHD symptoms, a 12 month reintroduction phase is needed to find out specifically which products trigger ADHD symptoms.

However, the ED studies showed large disparity in effect sizes. Results of studies which reported larger effect sizes [14] were questioned for several reasons [15–17]. A main concern was the nature of the control condition. This condition involved non-obligatory healthy food advice with no constraints and instructions for changing dietary habits compared with the ED group. Therefore, the control group differed essentially from the ED group regarding time investment, impact on family structure and parental treatment expectations. In addition, given that observational studies showed that unhealthy dietary patterns are associated with a higher risk of ADHD [18, 19], it remained unclear what caused the observed intervention-effect: specific elimination of certain foods or an overall general improvement of nutritional quality of the child’s diet. Thus far, no studies have examined the effects of an ED and a healthy diet (i.e. with different impact on nutritional intake), but with comparable impact on non-specific factors (e.g. time investment). By creating equivalent non-specific factors in both groups, it would be possible to examine the impact of nutritional intake only. A second concern was that the long-term effects (e.g. after one year) and feasibility of an ED are unknown. There are concerns about, for example, the nutritional quality of the diet, potential risks of nutritional deficiencies in the long term or the high burden it can place on the family. A third concern was that there are no studies reporting on the cost-effectiveness of an ED. A dietary treatment may be cost-effective: treatment expenses may be limited to once-only costs for a relatively short trajectory (in contrast with for example medication). A final concern was that earlier studies suffered from unsatisfactory blinding. Primary outcome measurements were based on a blinded pediatrician’s clinical judgment who based his judgment on the non-blinded information provided by parents. Expectation bias originating from parents and/or pediatricians may have influenced the outcomes.

To address these issues, the ‘Treatment of ADHD with Care as usual versus an Elimination diet’ (TRACE) study has been developed. This is the first RCT (two armed, 50:50 ratio) to determine the short- and long-term effectiveness and cost-effectiveness of an ED compared to an active control group (a healthy diet). Care As Usual (CAU) is included as a comparator arm. During the initial 5 weeks of the study, participants receiving a dietary treatment are not allowed to start any other treatment. Also, medication prior to the dietary treatment has to be discontinued no later than 1 week before start of the diet. The study will examine effects on both ADHD and emotion dysregulation, given that an ED showed equal effects on ADHD and its common comorbidity Oppositional Defiant Disorder (ODD) (i.e. children with ODD are more likely to experience emotion dysregulation problems) [14]. We will substantially improve upon previous studies by comparing an ED with a healthy diet (based on the World Health Organization (WHO) guidelines), comparing the two dietary treatments with CAU, examining the short- and long-term effects (i.e. after 5 weeks and 1 year) and cost-effectiveness, measuring the nutritional quality of the consumed diets and including blinded and objective measurements.

The primary objective of the TRACE study is to quantify the short-term (after 5 weeks) effectiveness in reducing ADHD and emotion dysregulation symptoms of an ED compared to an active control group (a healthy diet) in children aged 5–12 years with ADHD: we assume that the ED is more effective than the healthy diet. Secondary, the study aims at examining the long-term (after 1 year) effects in reducing ADHD and emotion dysregulation symptoms. Moreover, the study aims at examining the short- and long-term effects of an ED compared to an active control group (a healthy diet) in reducing secondary outcome measures related to ADHD such as cognitive outcomes, motor activity and sleep pattern. In addition, the study aims to identify potential moderators and mediators (e.g. socioeconomic status (SES), ethnicity, comorbidity) of the short- and long-term response to dietary treatments, and to examine the nutritional quality of the attained diet and health of children treated with a dietary treatment compared to CAU. Finally, the study aims to examine the cost-effectiveness of the dietary treatments compared with CAU.

## Methods

### Participants

Families are recruited at two clinical centers in the Netherlands: Karakter Child and Adolescent Psychiatry (Nijmegen) and Triversum - GGZ-NHN Child and Adolescent Psychiatry (Alkmaar). Researchers will screen files of patients (after consent of parents and/or psychiatrists) within these centers in order to check for eligibility or psychiatrists will refer the patients to the study. In addition, participants are recruited at the national level via advertisements, newspapers, the TRACE website, flyers and social media. Moreover, general practitioners, dieticians and other psychiatric institutions act as ambassadors and collaborate in the recruitment process by referring patients to the study. At the Nijmegen site, there is a team of certified clinicians who can diagnose (if necessary) participants recruited outside the participating centers.

For eligibility, participants must meet the following criteria: ADHD diagnosis according to the DSM-5 (any presentation) and 5–12 years old at the inclusion date. Comorbidities are allowed except for eating disorders (i.e. anorexia or bulimia nervosa) and diabetes mellitus. Exclusion criteria are insufficient mastery of Dutch language in parents or children; current treatment for ADHD that cannot be discontinued; significant parent-child relationship problems requiring family therapy; unwillingness to have meat or animal food products in the diet (without these products it is impossible to achieve nutritional adequacy of the overall diet for participants in the ED group). The CAU participants need to fulfill the same inclusion- and exclusion criteria.

One of the inclusion criteria includes an ADHD diagnosis. To confirm this diagnosis, children are screened by the researchers via a structured psychiatric interview with the parents based on the DSM-IV (Kiddie Schedule for Affective Disorders and Schizophrenia: K-SADS) [20]. The ADHD section and the ODD section of this interview are used. The latter is used to check for comorbidities. Also, teachers fill out the Strengths and Weaknesses of ADHD-symptoms and Normal-behaviors (SWAN) rating scale [21]. To confirm the clinical ADHD diagnosis, there should be a minimum of six out of nine symptoms present in at least one domain (i.e. hyperactivity/impulsivity or inattentiveness), based on parent and teacher ratings. Parents and teachers have to separately rate at least four out of nine symptoms in one domain. Children are not able to participate if this criterion is not met.

### Study design

#### Randomization

Originally, the TRACE study was a three arm randomized controlled trial: participants were randomized to an elimination diet, healthy diet or CAU. However, randomization across a dietary intervention versus CAU proved not feasible. Parents usually had a strong preference towards either a dietary intervention or CAU. This resulted in an extremely slow inclusion rate, a high number of drop-outs and thereby unrepresentative groups of CAU. Therefore, after inclusion of 17 participants, the design was changed into a two arm randomized controlled trial (elimination diet vs. healthy diet) with a non-randomized comparator arm (CAU). Participants interested in a dietary intervention are randomized (50:50) to either an ED or a healthy diet with randomization within each participating center. Randomization by means of minimization is performed, including sex and age as factors, resulting in four groups. Within each group, blocked randomization is used (block size eight). The non-randomized comparator arm includes children who are being treated with CAU. Researchers disclose the group allocation to parents via a sealed envelope. Participants, researchers and dieticians are aware of treatment allocation. Researchers who will code the behavior observation (see secondary outcomes) are blinded to group allocation and time of assignment.

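### The article names two incompatible allocation methods, minimization and fixed blocks of eight; if blocks were used, unblinded recruiting staff could partly predict the next diet.

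*Protocol article*

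**What the plan says.** All statements are in the protocol article.

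- **Method.** The Randomization section says "Randomization by means of minimization is performed, including sex and age as factors, resulting in four groups". Its next sentence says "Within each group, blocked randomization is used (block size eight"). One block size is given, with no mention of variation.
- **Ratio and centres.** Children are "randomized (50:50) to either an ED or a healthy diet with randomization within each participating center".
- **Who knows the allocation.** "Participants, researchers and dieticians are aware of treatment allocation". Only the coders of the behaviour observation are blinded.
- **Who meets the families.** Under Participants, "Researchers will screen files of patients (after consent of parents and/or psychiatrists) within these centers in order to check for eligibility", and "children are screened by the researchers via a structured psychiatric interview with the parents". Under Procedures, families who meet the criteria come to an intake with a researcher, where the diet is disclosed. The Randomization section adds: "Researchers disclose the group allocation to parents via a sealed envelope".

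The article does not say who generates or holds the allocation sequence. A condensed article may leave that out, and it is not counted against the plan here.

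**The concern.** Two problems come together.

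First, minimization assigns each child by the running imbalance across factors. It does not form groups with separate blocks inside them. Permuted blocks within sex-by-age groups are stratified blocked randomization. Both sentences cannot describe the method in use, and a reader cannot tell which one is right.

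Second, a sealed envelope hides its own contents but not what the earlier allocations imply. With a fixed 4:4 block, once four children in a stratum have received one diet, the rest of that block is determined. An independent list holder would not remove this, because the inference needs only past allocations and the block size.

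The design makes concealment matter more than usual. The primary outcome rests on parent and teacher ratings, and the article says that participants know their allocation. The blinded observation is only a secondary outcome. Staff who could foresee the next diet would have some room to act on it. They schedule the intake, and some exclusions need judgement, such as relationship problems that call for family therapy or ADHD treatment that cannot be stopped. Intention-to-treat analysis does not repair selection that happens before allocation.

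**Working it through.** **Inputs.** Block size 8 and ratio 1:1, so m = 4 places per diet (Randomization). Two centres (Participants) and four sex-by-age groups, so 2 × 4 = 8 strata. Total 2 × 81 = 162 randomised children (Sample size and power).

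The article gives no figure for predictability, so there is none to reproduce. Its power figures (0.99 and 0.64) do reproduce from the Table 4 counts, at 0.991 and 0.645, but they do not bear on this point.

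**Step 1: allocations that are certain in a completed block.** There are C(8,4) = 70 possible blocks. A place is certain when all places from it to the end of the block go to the same diet.

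| Place | Blocks in which it is certain | Share |
|---|---|---|
| 1st to 4th | 0 of 70 | 0% |
| 5th | 2 × C(4,0) = 2 | 2.9% |
| 6th | 2 × C(5,1) = 10 | 14.3% |
| 7th | 2 × C(6,2) = 30 | 42.9% |
| 8th | 2 × C(7,3) = 70 | 100% |

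The sum is 112/70 = 1.6 per block, which agrees with 2m/(m+1) = 8/5. As a share, 1.6/8 = 20%.

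**Step 2: allocations that can be guessed in a completed block.** The best guess always names the diet with more places left, and tosses a coin when they are equal. Expected correct guesses are m + (2^(2m)/C(2m,m) − 1)/2 = 4 + (256/70 − 1)/2 = 5.33 of 8, or 66.6%. Simple randomization gives 50%.

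**Step 3: the whole trial.** Multiplying 162 by 20% gives 32, but that treats every block as complete. With 162/8 = 20.25 children per stratum, most strata end part-way through a block, and the first four places of a block are never certain. Two full blocks in each of eight strata give 8 × 2 × 1.6 = 25.6. Simulation of 162 children, with stratum sizes varying by chance and incomplete last blocks included, gives:

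| Assumption | Certain | Correct guesses |
|---|---|---|
| 8 equal strata | 27.6 (17.0%) | 105.5 (65.1%) |
| 8 uneven strata (centres 70:30, sex 75:25) | 27.4 (16.9%) | 105.5 (65.1%) |
| 4 strata, centre ignored | 30.0 (18.5%) | 106.7 (65.8%) |

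Chance alone gives 81 correct guesses, so the excess over eight strata is 105.5 − 81 = 24.5, about 24 to 25. The share that is not certain is 100% − 17% = 83%.

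**The case against.** The strongest reply is that the text shows less than it seems to. A reader might infer that the researchers run the allocation themselves and that each of them knows every earlier assignment. The article says neither. It says that researchers are aware of allocation and hand over the result. It does not say that one person both screens and discloses, or that anyone tracks the ordered sequence within a stratum. That objection stands, so the figures are conditional.

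The figures also presuppose blocks. The mention of minimization leading to four groups may be a loose term for stratification, which would support the block reading. If true minimization was used, however, none of the block arithmetic applies. This stands as well, but it does not rescue the paragraph: one of the two sentences would still be wrong.

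A reader might further infer that staff would steer motivated families towards the elimination diet because it is the heavier burden. The documents do not support this. Motivation is not an eligibility criterion, and diagnostic confirmation needs symptom counts from both parents and teachers. Families choosing a dietary arm accept randomization to either diet, and the Healthy diet section describes a strict regimen meant to match the elimination diet in its impact on the family. The direction of any bias is therefore unknown, and no effect on the odds ratio has been estimated.

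Finally, Procedures already places the eligibility check before the intake at which the diet is disclosed. What it leaves unclear is whether consent is recorded before disclosure.

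**Conclusion.** The contradiction between minimization and blocks holds on the text alone and needs correction.

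The predictability point holds conditionally. It assumes that blocks of eight are what is used, that recruiting staff know the size, and that they can follow the order of entry within strata. On those assumptions about 27 to 28 of 162 allocations (17%) could be known in advance, and guessing would be right about 24 to 25 times more often than by chance. It would be wrong to conclude that upcoming diets are generally predictable: more than four in five allocations cannot be known with certainty, and certainty arises mostly at the seventh and eighth places of a block.

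This is an avoidable risk of selection bias in the comparison of the two diets. Nothing in the article shows that selection took place. The point deserves action but does not undermine the design.

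**What to change.** 1. Correct the Randomization section so that it names one method. State which method was used for children already allocated and, if it was blocks, whether the size varied.
2. For children still to be randomised, use randomly varying block sizes that are not disclosed to recruiting staff, or true minimization with a random element. Because the size of eight is now published, withholding it is no longer enough; the sizes themselves must change.
3. State that an allocation is released only after both eligibility and consent are recorded.

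**Cost.** A new allocation list and a short amendment, with no extra children or visits. Imbalance within small strata may become slightly larger, and a mid-trial change of method has to be documented. The gain is limited to the remaining recruitment: the article appeared in May 2020 and expects recruitment to finish in December 2020. The correction in item 1 is worthwhile however few children remain.

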#### 1st phase: five weeks

During the initial 5 weeks of the study, participants receiving a dietary treatment are not allowed to start treatment with medication or to receive specific psychosocial interventions other than psychoeducation in a group setting. If participants choose otherwise, this is coded as non-compliance. Similarly, participants receiving CAU are not allowed to follow a strict dietary advice. If they choose otherwise, this is coded as non-compliance. Non-compliant participants will still be assessed during the follow-up measurements.

#### 2nd phase: five weeks until 12 months after baseline

After 5 weeks, response to treatment is evaluated comparing measures of ADHD symptoms (i.e. SWAN questionnaire) and emotion dysregulation symptoms (i.e. SDQ questionnaire: dysregulation profile) before and after the 5 weeks (see Method section, primary outcome paragraph ‘respondership’). Full and partial responders (see primary outcome ‘respondership’) to the dietary treatment are invited to continue the diet in the second phase of the study until the end of the trial (12 months after baseline). Mixed responders (see primary outcome ‘respondership’) are offered to continue the diet, but are not explicitly advised as with the full and partial responders. To optimize the generalizability and feasibility of the study results to clinical practice, participants on the diet-trajectory are allowed to stop the diet switch to CAU after 5 weeks. This will be advised when participants do not respond to the diet (i.e. non-responders and deterioration group). Responders are allowed to add CAU to the diet, but this will not be advised as with the non-responders. Participants in the comparator arm will not be offered the possibility to switch to one of both dietary interventions to allow unbiased examination of (cost) effectiveness of the diet-trajectories.

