### Procedures

Families who are interested to participate in the TRACE study are informed via telephone and information letters (sent via e-mail). Families can choose whether they want to participate in the dietary treatment arms or the CAU arm. If they choose a dietary treatment, they will be randomly assigned to either the elimination diet or the healthy diet.

If the eligibility criteria are met, parents are invited for an intake with a researcher to explain further details of participation, plan appointments and to disclose which diet the child is randomized to via a sealed envelope. Both parents fill out a written informed consent for the TRACE study (Additional file 1). If children are 12 years old, they also need to sign the consent forms. In addition, teachers are informed about the study via e-mail and general practitioners via postal letters.

Assessments will take place at baseline (T0), after five weeks of treatment (T1), after four (T2), eight (T3) and 12 (T4) months after start of treatment (i.e. dietary treatment or CAU). T0 will be scheduled within two weeks prior to the start of the treatment. Medication treatment prior to the dietary treatment has to be discontinued no later than one week before start of the diet. T0, T1 and T4 assessments will take place at one of the two participating sites. For the T2 and T3 assessments, parents are asked to fill out questionnaires online. Teachers are asked to fill out online questionnaires at T0, T1 and T4. Figure 1 depicts a flowchart on recruitment and procedure of the study.

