For the cost-effectiveness analysis, all cost data will be accumulated over the 12 months period. Cost differences between the two dietary conditions and CAU will be compared. Incremental cost-effectiveness ratios will be calculated by dividing cost differences between treatments by differences in Quality Adjusted Life Years, as estimated from EQ-5D scores. Uncertainty analysis using 5000 bootstraps will be performed and cost-effectiveness planes and cost-effectiveness acceptability curves will be plotted.

The impact of missing data on the outcome measurements will be evaluated using different methods, such as Last Observation Carry Forward (LOCF) and Multiple Imputation (MI).

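### Not offering CAU families a diet limits contamination but does not make the 12-month diet-versus-CAU cost-effectiveness comparison unbiased, because families choose their arm and no adjustment is named

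*Protocol article*

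**What the plan says.** Under the heading for the second phase (five weeks to 12 months), the protocol article explains why CAU participants may not move to a diet: "to allow unbiased examination of (cost) effectiveness of the diet-trajectories".

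Three other places bear on that clause.

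- **How children enter CAU.** Procedures: "Families can choose whether they want to participate in the dietary treatment arms or the CAU arm". The Randomization section says that the three-arm randomised design was abandoned after 17 inclusions, that CAU is now non-randomised, and why: "Parents usually had a strong preference towards either a dietary intervention or CAU".
- **What the economic analysis compares.** The last aim in Background and the Cost measurements section both set the diets against CAU, the latter at 12 months. Statistical analyses: "Cost differences between the two dietary conditions and CAU will be compared". Background also presents the trial as determining the cost-effectiveness of ED against the healthy diet, which is the randomised contrast.
- **How it is computed.** The incremental ratio comes from "dividing cost differences between treatments by differences in Quality Adjusted Life Years", with QALYs estimated from EQ-5D. Then: "Uncertainty analysis using 5000 bootstraps will be performed". No covariate, weighting or matching is mentioned for this analysis.

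**The concern.** A bar on crossover and the way children come to be in an arm deal with different biases. The bar stops CAU children from receiving a diet during follow-up. It cannot make families who wanted CAU comparable with families who wanted a diet. They may differ in baseline quality of life, severity, medication history, socioeconomic status and use of care, and each of these can affect 12-month costs or QALYs whatever the diet does. The clause would suit a randomised CAU arm. It does not suit the current one.

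The diet-versus-CAU result is the trial's main economic output, and the stopping rule under Data monitoring is also justified by whether the diets could match CAU on effect and cost-effectiveness. If the ratio is computed as literally described, any lasting family difference enters the ratio, the cost-effectiveness plane and the acceptability curve. None of these shows that source of error.

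**Working it through.** The article states no figure for diets versus CAU, so there is nothing to reproduce. The point rests on the text; the arithmetic only shows scale.

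**Step 1: the text.**

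| Question | Protocol article | Consequence |
|---|---|---|
| What does the no-switch rule control? | Exposure to diet within CAU (2nd phase) | Less contamination |
| What decides diet or CAU? | Family choice (Procedures; Randomization) | Groups need not be comparable |
| What decides ED or healthy diet? | Randomisation within centre | Comparable in expectation |
| Is adjustment named for the ratio? | No (Statistical analyses, cost-effectiveness paragraph) | Confounding not addressed as described |
| Is adjustment named elsewhere? | ANCOVA with the T0 value as covariate, for continuous outcomes at T1 | Not linked to the 12-month ratio |
| Are baseline differences checked? | Prior beliefs are compared across all three groups, as a check on randomisation | Not fed into any analysis; CAU is not randomised |

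**Step 2: what the bootstrap covers.** Write the observed difference as true effect + selection difference + sampling error. Resampling children within the groups as formed reproduces only the last term. The first two stay together in the centre of the bootstrap distribution.

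**Step 3: sampling error (SD assumed).** From the article: 81 per diet, 60 in CAU. The utility or QALY SD is not given; take 0.15 to 0.20.

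- SE = SD × √(1/81 + 1/60) = SD × 0.1703
- SD 0.20: SE = 0.034; 95% half-width 1.96 × 0.034 = 0.067
- SD 0.15: SE = 0.026; 95% half-width 0.050

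**Step 4: a lasting selection gap g in QALYs, with no true diet effect (g assumed).** The chance that the 95% interval excludes zero is 1 − Φ(1.96 − g/SE) + Φ(−1.96 − g/SE).

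| g | SD 0.15 | SD 0.20 |
|---|---|---|
| 0 | 5% | 5% |
| 0.02 | 12% | 9% |
| 0.05 | 50% | 31% |
| 0.08 | 88% | 65% |

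**Step 5: the ratio (all inputs assumed).** Ratio = (ΔC + cost bias)/(ΔQ + QALY bias). Take true ΔC = 1,000 euros and ΔQ = 0.03, so the ratio is 1,000/0.03 = 33,333 per QALY. Let the cost bias run from −500 to +500 and the QALY bias from −0.02 to +0.02.

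- Lowest: (1,000 − 500)/(0.03 + 0.02) = 10,000
- Highest: (1,000 + 500)/(0.03 − 0.02) = 150,000
- A QALY bias of −0.03 leaves a zero denominator, and a larger negative bias changes the sign.

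These figures show that the ratio is sensitive to modest lasting gaps. They do not show that such gaps exist in this trial.

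**The case against.** The best defence is that the disputed clause justifies a single rule, the bar on switching, and read in place it means no more than keeping the comparator clean. The article openly calls CAU non-randomised, explains why, and nowhere attaches the word to the ratio itself. This stands in part: it is an overclaim in one clause, not concealment. But the clause names (cost-)effectiveness of the diet trajectories as what is examined without bias, and the rule cannot deliver that.

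A reader might infer that the plan commits to raw, unadjusted differences. The document does not say so. It gives the usual definition of the ratio and is silent on adjustment, and a fuller analysis plan that is not shown may add it. What can be said is that following the text as written gives an unadjusted ratio. Adjustment elsewhere would reduce the bias but would not make the clause true.

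A reader might also infer that the analysis would show falsely narrow uncertainty. At these sample sizes it would not. With SE 0.034, an assumed gain of 0.03 has a 95% interval of 0.03 ± 0.067, about −0.04 to 0.10. The fault lies in where the interval is centred and which error it omits. Chance imbalance between arms is no evidence of confounding either, since the bootstrap does capture it.

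Finally, one might infer that ED versus healthy diet has been dropped from the economic analysis. Background states both aims, and the reference to differences between treatments could cover both contrasts. The cost sentence, however, names only diets versus CAU.

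**Conclusion.** The point holds in limited form. The clause claims more than the no-switch rule can give. The diet-versus-CAU economic comparison is observational, and the analysis described names nothing to deal with selection. This follows from the text and needs no assumed input.

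The size and direction of any bias cannot be derived from the document. The figures above rest on assumed SDs, effects and gaps, and on those gaps lasting 12 months. ED versus healthy diet is not affected. The point deserves a change before analysis and has no bearing on the stated sample size or power.

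**What to change.** 1. In the second-phase section, replace the claim of unbiased examination with a statement that the rule avoids contamination of CAU by diet.
2. Report the ED-versus-healthy-diet ratio as the randomised economic result, alongside diets versus CAU.
3. For diets versus CAU, estimate the cost and QALY differences within each of the 5000 bootstrap samples by regression or weighting on T0 EQ-5D, SWAN, SDQ, age, sex, centre, SES, prior beliefs and, where recorded, prior medication.
4. Label that result non-randomised wherever it appears, including the plane and the acceptability curve.

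**Cost.** Slightly more programming. Apart from prior medication, which is conditional on being recorded, these variables are already collected, and none is among the measures that Measurements CAU says are dropped for that arm. No change to sample size or procedures is needed.

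**Downside.** Residual confounding must be stated, with two specific limits. Table 3 lists the cost questionnaire from T1 only, so there is no baseline cost to adjust for. T0 falls within two weeks before treatment starts, while diet children may stop medication as late as one week before the diet, so T0 ratings may be made on or off medication, and this may differ between the diet and CAU groups.
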